#### 2.7.2. Secondary Outcomes

##### The International Prostate Symptom Score (IPSS)

This is a 7-point scale for assessing the symptoms of benign prostatic hyperplasia (BPH). Seven questions focus on the symptoms of BPH. Rating: 0–7 mildly symptomatic, 8–19 moderately symptomatic, and 20–35 severely symptomatic. One question focuses on quality of life. On the scale, 0 = delighted, 1 = pleased, 2 = moderate symptoms, and 5 = severe symptoms. Cronbach’s alpha IPSS ≥ 0.60 and ≥0.79, respectively. The intra-class correlation coefficient was high (≥0.59) [14,15].

##### Overactive Bladder Questionnaire (OAB-q)

This questionnaire focuses on the symptoms of OAB incontinence in the last 4 weeks. It contains 6 questions with symptom scores (0 without symptoms, 100 most symptoms) and 13 questions that evaluate quality of life (100 best quality of life, 0 worst quality of life). Cronbach’s alpha OAB-q is 0.90 [16,17]. The Overactive Bladder Symptom Score (OABSS) has 7 questions and 5 answers. It is used to examine the symptoms of an overactive bladder. Total score is 0 = no symptoms, and 28 = severe symptoms. Spearman’s correlation coefficient was 0.84 [18].

##### Patient Global Impression of Improvement Score (PGI-I)

Condition of urination problems compared to the condition before a patient started treatment in the study. Scores: 1 = much better, 2 = quite better, 3 = a little better, 4 = no change, 5 = a little worse, 6 = a lot worse, and 7 = much worse [19].

##### Incidence of Adverse Events

Monitoring of treatment side effects and serious side effects. Very common side effects are ejaculatory disorders, including retrograde ejaculation and anejaculation. Common side effects are dizziness, orthostatic hypotension, nasal congestion, and diarrhea [20].

### 2.8. Adherence

Competence, cooperation, and security will be recorded during the recruitment and implementation of the study. The principal investigator, in collaboration with urologists, will register suitable patients from all databases in outpatient clinics and registries. The number of eligible patients from all enrolled patients will be recorded. During the intervention period, cooperation and therapeutic adherence to the exercise regimen and drug treatment, as well as treatment interruption, will be recorded in the diary. 

### 2.9. Statistical Analysis

Descriptive and inferential statistics will be used for data analysis. The unpaired t-test will be used to compare the experimental and control groups before training. Our data will have a normal distribution. Differences between control and experimental groups before and after the intervention will be evaluated by General Linear Model (GLM), Mixed Design ANOVA—repeated measurements with Greenhouse–Geisser correction. The significance level will be set at 95%, *p* < 0.05. Effect size (ES) will be calculated based on the Partial Eta Squared (η^2^). According to Cohen, the specification for ANOVA analysis of small, medium, and large effect size will be classified as η^2^: 0.00–0.003: no effect size; η^2^: 0.010–0.039: small effect size; η2: 0.060–0.110: medium effect size; η^2^: 0.140–0.200: large effect size. Calculations will be performed in IBM SPSS Statistics for Macintosh, Version 27.0 (IBM Corp., Armonk, NY, USA).

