### 2.3. Sample Size Estimation

We used an estimate made by sampling the number of probands based on a power of test using 0.80 and alpha 0.05 (type I error). Using a statistical program, we determined the calculation of the number of probands; there will be 63 in the experimental group and 63 in the control group. We expect a 20% loss, so we will include at least 158 probands. According to the sample selection, we expect a 20% decrease in incidence after the intervention.

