## Figures and Tables

**Table 1 ijerph-18-11426-t001:** Recruitment, intervention, and evaluation plan for the experimental and control groups in the Silodosing study.

Time Period	Enrolment (T0) before Treatment (T1)	After 12 Weeks of Treatment (T12)
Informed consent	x	
Enrolment	x	
Allocation	x	
Demographic data	x	
Voiding diary	x	x
The International Prostate Symptom Score (IPSS)	x	x
Overactive Bladder Questionnaire (OAB-q)	x	x
Overactive Bladder Symptom Score (OABSS)	x	x
The Patient Perception of Intensity of Urgency Scale (PPIUS)	x	x
Patient Global Impression of Improvement score (PGI-I)		x
Adverse events—harms	x	x
Adherence	x	x
Intervention for experimental group	x	x

**Table 2 ijerph-18-11426-t002:** Exercise program for men with BPH and OAB.

	Description	Dosage
1	Education about proper urination training in the period without pathological urgency. Education about conscious urgency suppression through PFMT—the suppressive urgency technique. Education about healthy urge to urinate and pathological urge to urinate. Education on how to cancel a sudden, urgent urge to urinate: a. Tighten the rectal muscles and pull them as if inside the body and hold on until the urge to be in your current position is lifted; b. If you cannot keep your rectal muscles tightened, for 2 s, release them and download them again.	5 times
2	Education on the principle and effect of PFMT. Do not contract the sciatic muscles, abdominal muscles, and lower limbs instead of the rectal muscles. The principle of exercise: by compressing the muscles of the rectum and pulling them as if inside the body, you also affect the muscles around the urinary tract.	5 times
3	Education about proper ergonomics during everyday activities. Education about the correct breathing stereotype. When lying on your back or sitting, keep your chest in an exhaled position. With a breath to the sides of the abdomen, you activate the correct diaphragmatic breathing. With exhalation, pull the navel to the spine, activating the deep abdominal muscles.	5 times
4	Exercise Phase 1: Weeks 1 and 2 Exercise 1: Pelvic floor muscle awareness Exercise positions: Lying on the back—legs bent, lying on the abdomen, then sitting, standing. Exercise: Awareness of the rectal muscles. Inhale—imagine that you want to draw the rectal muscles inside the body and exhale and relax the rectal muscles, in the rhythm of normal breathing, repeat 10–20 times.	15 min a day

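### The mixed ANOVA on two occasions is only a change-score t test; adjusting for the baseline already collected would be more precise at no cost

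*Protocol article*

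**What the plan says.** Section 2.9 gives one method for comparing the arms on outcome: "Differences between control and experimental groups before and after the intervention will be evaluated by General Linear Model (GLM", specified as a mixed-design ANOVA for repeated measurements with Greenhouse–Geisser correction. Effect size is to be partial eta squared. No baseline covariate is mentioned. The only other test named is confined to baseline: "The unpaired t-test will be used to compare the experimental and control groups before training".

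Table 1 has two assessment columns. One covers enrolment and the time before treatment (T0 and T1 together). The other is headed "After 12 Weeks of Treatment (T12". The voiding diary, PPIUS, IPSS, OAB-q and OABSS are each marked in both columns.

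Sections 1.1 and 2.7.1 define the primary outcome as the change in the number of voidings and in the intensity of urgencies over 24 hours, taken from a 3-day diary.

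**The concern.** A repeated-measures model with a sphericity correction suggests several follow-up occasions. This trial has one baseline and one follow-up value per man. The model therefore reduces to comparing mean change between arms, and the correction has nothing to act on.

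Comparing raw change subtracts the whole baseline value, whatever its correlation with week 12. When that correlation is modest, the subtraction adds noise. ANCOVA subtracts only the part of the baseline that predicts the outcome. What is at stake is precision on the primary outcome: a wider interval and lower power than the same men and the same diaries could give. Section 2.9 also does not say which term of the model carries the treatment comparison.

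**Working it through.** **Inputs from the article.** Section 2.3, on error rates: "power of test using 0.80 and alpha 0.05 (type I error". On evaluable numbers it says that "there will be 63 in the experimental group and 63 in the control group". It allows for losing 20% and sets a recruitment minimum of 158. Table 1: two occasions. Section 2.9: no baseline covariate.

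**Assumptions not in the article.** Two-sided alpha; a between-arm effect of 0.5 in units of the week-12 SD; equal SDs before and after; rho varied.

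**1. The plan's own figures.** The loss step reproduces: 126/(1 − 0.20) = 157.5, rounded up to 158. The 63 per arm cannot be rebuilt from what is stated. The only effect given is that "we expect a 20% decrease in incidence after the intervention", with no starting rate, mean difference or SD. A standardised difference of 0.5 does return it: 2 × (1.960 + 0.842)² / 0.5² = 62.8, so 63 (64 by the exact t calculation). Some pairs of proportions 20 points apart come equally close (62 for 30% v 10%, 64 for 31% v 11%). The 0.5 SD is therefore a working assumption, not the sponsor's stated effect.

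**2. Interaction equals change-score test.** With two occasions, the group-by-time contrast is mean change in one arm minus mean change in the other. On one simulated data set with 63 per arm, the interaction F was 11.7416 on 1 and 124 df, and the squared unpaired t on change was 11.7416, giving the same p-value.

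**3. The correction is idle.** Greenhouse–Geisser epsilon lies between 1/(k − 1) and 1 for k occasions. At k = 2 it must be 1. Two covariance matrices with unequal variances both gave 1.0.

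**4. Variance per man, in units of SD².** Change score: 2(1 − rho). ANCOVA: 1 − rho². Ratio: (1 − rho²)/[2(1 − rho)] = (1 + rho)/2. With unequal SDs, the change-score variance exceeds the ANCOVA variance by (SD_pre − rho × SD_post)², which is never negative.

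**5. Power at 63 per arm, effect 0.5 SD.** The standard error is √(2v/63), with v the variance from step 4. At rho 0.5, for example, the change score has v = 1.00, SE 0.178 and 0.5/0.178 = 2.81. ANCOVA has v = 0.75, SE 0.154 and 0.5/0.154 = 3.24.

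| rho | v, change | v, ANCOVA | ratio | power, change | power, ANCOVA | n per arm for 80%, change v ANCOVA |
|---|---|---|---|---|---|---|
| 0.3 | 1.40 | 0.91 | 0.65 | 65.3% | 83.1% | 88 v 58 |
| 0.5 | 1.00 | 0.75 | 0.75 | 79.5% | 89.5% | 63 v 48 |
| 0.7 | 0.60 | 0.51 | 0.85 | 94.9% | 97.4% | 38 v 33 |
| 0.8 | 0.40 | 0.36 | 0.90 | 99.3% | 99.7% | 26 v 23 |

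Power in the first three rows uses the t distribution. The last row and the n column use the normal approximation, which gives 80.1% and 90.0% at rho 0.5. Simulation with 4,000 runs agreed: 64.9% v 83.2%, 79.7% v 89.7% and 94.6% v 97.4% at rho 0.3, 0.5 and 0.7. Simulated type I error was near 5% for both methods (0.049 to 0.058).

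Below rho 0.5, the change score is less precise than ignoring baseline altogether. At rho 0.3, comparing T12 values alone has 80.1% power against 66.0% for change (both by normal approximation).

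**The case against.** The strongest reply is that nothing here is an error. The primary outcome is defined as change, a change-score comparison answers that question, and under randomisation it is unbiased with the right type I error. That stands: the cost is precision only. It also stands that the size of the gain rests on two figures the article does not give, and that the gain nearly vanishes at high rho. Section 2.4 admits men by diary thresholds. If that narrows the baseline spread, the equal-SD formula is only approximate, and the gap may be smaller than tabulated.

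The reply does not remove the point. The article fixes an unadjusted model rather than leaving the choice open, and in large samples ANCOVA is never the less precise of the two.

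A reader might infer more, which the article does not support:

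- **That the planned model would be forced onto outcomes it cannot fit.** Table 1 marks "Patient Global Impression of Improvement score (PGI-I" at T12 only, so no before–after model could be fitted to it. But section 2.9 applies the model to differences before and after the intervention, and does not assign PGI-I or adverse events to it. An article may leave the tests for those outcomes to the full plan.
- **That the treatment effect will be read from the group main effect.** That term averages baseline with week 12 and so halves the effect (simulated power 42%, 37% and 33% at rho 0.3, 0.5 and 0.7). No section says it will be used, and the change outcome in sections 1.1 and 2.7.1 points to the interaction.
- **That the idle correction or the baseline t tests damage the result.** Removing either changes no efficacy result.
- **That a clinic random intercept is required.** With 126 evaluable men over 45 clinics (126/45 = 2.8 each), its value is debatable.

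**Conclusion.** The point holds as a matter of efficiency. For outcomes measured twice, the stated model is a change-score t test with an idle correction, and it forgoes precision that the baseline value would give.

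Under equal SDs the variance saved is 35%, 25% and 15% at rho 0.3, 0.5 and 0.7. At 63 per arm and 0.5 SD, the power gained is about 18 points at rho 0.3, 10 at rho 0.5, 2 to 3 at rho 0.7 and under 1 at rho 0.8. The identity with the change-score test and the idle correction need no assumption beyond two occasions. If T0 and T1 were in fact separate assessments there would be three, but Table 1 shows them as one column.

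It would be wrong to conclude that the planned analysis is biased or invalid, or that the trial is underpowered. The article gives neither the effect nor the correlation needed to say the latter.

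**What to change.** In section 2.9, for the diary outcomes and for IPSS, OAB-q and OABSS, make the between-arm analysis an ANCOVA of the T12 value on arm and the baseline value of the same variable. Report the adjusted mean difference with its 95% CI. If the mixed ANOVA is kept, state that the group-by-time term is the test of treatment effect.

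The cost is a change of wording, best made before any outcome is seen by arm. Table 1 already collects every variable needed; no visit, form or patient is added.

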## 3. Conclusions

The study protocol presents the starting points and design of a randomized, interventional, multicenter study monitoring the effect of combination therapy with silodosin and pelvic floor muscle training (PFMT) in comparison with silodosin treatment alone in men with BPH and OAB. The study may provide evidence of the efficacy of combined treatment for OAB and indicate an active approach for the treatment of OAB through exercise. The strength of the study is that it promotes a non-invasive and conservative treatment of strengthening pelvic floor muscles with the suppressive-urgency technique in addition to silodosin treatment. We will use standardized measuring tools: the voiding diary for the assessment of changes in the number and intensity of urgencies over 24 h [1], the Patient Perception of Intensity of Urgency Scale (PPIUS) [13,19,21], the International Prostate Symptom Score (IPSS) for the assessment of prostate symptoms [13,14], the Overactive Bladder Questionnaire (OAB-q) for assessing changes in incontinence quality of life [16,17], the Overactive Bladder Symptom Score (OABSS) to examine the symptoms of an overactive bladder [18], and the Patient Global Impression of Improvement score (PGI-I) to assess the condition of urinary problems compared to pre-treatment [22].

The strength of the study is its support of the innovative non-invasive conservative treatments of pelvic floor muscle training and medication with silodosin in patients with BPH and OAB.

The Methodology section describes the ranking criteria, method of inclusion in the study, and randomization procedure. The patients will be men aged over 50 with BPH and OAB. Within that demographic, the following parameters will be monitored: age of probands, education, height, weight, employment, smoking, alcohol, hypertension, lung diseases, nervous diseases, cardiovascular diseases, and other diseases.

The intervention in both groups will be oral treatment with silodosin at a daily dose of 8 mg; in the experimental group, pelvic floor muscle training (PFMT) with the suppressive urgency technique will be added. Interventions will last 12 weeks, with exercises five times a week for 30 min a day, under the supervision of a physiotherapist. Education will consist of education about proper urination training in the period without pathological urgency, education about conscious urgency suppression through the PFMT suppressive urgency technique, education on the principle and effect of PFMT, education about proper ergonomics during everyday activities, education about the correct breathing stereotype, and education regarding the correct understanding of exercises by physiotherapists in cooperation with a nurse.

The program includes exercises about pelvic floor muscle awareness, exercises of varying intensity of pelvic floor muscles in different positions, and pelvic floor muscle relaxation exercises. Subsequently, the exercise will be performed at home with a diary check.

Based on similar studies, we expect good cooperation, small losses of probands, and agreement with the study protocol. Patients who are assigned to silodosin only will be offered the opportunity to exercise after 12 weeks of treatment. We assume a 20% loss. We will consider the success of the treatment to be a decrease of more than 50% in remission.

## Figures and Tables

**Table 1 ijerph-18-11426-t001:** Recruitment, intervention, and evaluation plan for the experimental and control groups in the Silodosing study.

Time Period	Enrolment (T0) before Treatment (T1)	After 12 Weeks of Treatment (T12)
Informed consent	x	
Enrolment	x	
Allocation	x	
Demographic data	x	
Voiding diary	x	x
The International Prostate Symptom Score (IPSS)	x	x
Overactive Bladder Questionnaire (OAB-q)	x	x
Overactive Bladder Symptom Score (OABSS)	x	x
The Patient Perception of Intensity of Urgency Scale (PPIUS)	x	x
Patient Global Impression of Improvement score (PGI-I)		x
Adverse events—harms	x	x
Adherence	x	x
Intervention for experimental group	x	x

**Table 2 ijerph-18-11426-t002:** Exercise program for men with BPH and OAB.

	Description	Dosage
1	Education about proper urination training in the period without pathological urgency. Education about conscious urgency suppression through PFMT—the suppressive urgency technique. Education about healthy urge to urinate and pathological urge to urinate. Education on how to cancel a sudden, urgent urge to urinate: a. Tighten the rectal muscles and pull them as if inside the body and hold on until the urge to be in your current position is lifted; b. If you cannot keep your rectal muscles tightened, for 2 s, release them and download them again.	5 times
2	Education on the principle and effect of PFMT. Do not contract the sciatic muscles, abdominal muscles, and lower limbs instead of the rectal muscles. The principle of exercise: by compressing the muscles of the rectum and pulling them as if inside the body, you also affect the muscles around the urinary tract.	5 times
3	Education about proper ergonomics during everyday activities. Education about the correct breathing stereotype. When lying on your back or sitting, keep your chest in an exhaled position. With a breath to the sides of the abdomen, you activate the correct diaphragmatic breathing. With exhalation, pull the navel to the spine, activating the deep abdominal muscles.	5 times
4	Exercise Phase 1: Weeks 1 and 2 Exercise 1: Pelvic floor muscle awareness Exercise positions: Lying on the back—legs bent, lying on the abdomen, then sitting, standing. Exercise: Awareness of the rectal muscles. Inhale—imagine that you want to draw the rectal muscles inside the body and exhale and relax the rectal muscles, in the rhythm of normal breathing, repeat 10–20 times.	15 min a day
5	Exercise Phase 2: weeks 3–12 Exercise 2: Exercises to strengthen the pelvic floor muscles Exercise positions: Spine, abdomen, sitting, semi-sitting, standing, walking (medium strength and very strong rectal muscle contraction). Exercise: a. Tighten the rectal muscles and pull them into the body moderately for 10 s and then relax for 10 s. b. Tighten the rectal muscles and pull them into the body very hard for 5 s and then relax them for 5 s.	15 min a day
6	Exercise 3: Pelvic floor muscle relaxation exercises Exercise positions: Lying on your back, then sitting. Exercise: a. Tighten the rectal muscles moderately for 1 s and then relax for 10 s. b. Tighten the rectal muscles slightly for 5 s and then relax for 10 s.	15 min a day

## Data Availability

We have not received ethical approval to share raw clinical trial data. The data that will be collected will be available upon request to the author.

## Abbreviations

PFMT	Pelvic floor muscle training
PGI-I	Patient Global Impression of Improvement
OAB-q	Overactive Bladder Questionnaire
OABSS	Overactive Bladder Symptom Score
PPIUS	The Patient Perception of Intensity of Urgency Scale
IPSS	The International Prostate Symptom Score
GLM	General linear model
ANOVA	Analysis of variance
